### Primary outcome measure

The primary outcome measure will be the pain domain of the Foot Health Status Questionnaire (FHSQ). The FHSQ consists of 13 questions reflecting four foot health-related domains: foot pain, foot function, footwear, and general foot health [66]. The FHSQ pain domain comprises four questions, with higher scores representing better foot health (that is, 100 = best foot health and 0 = worst foot health). The FHSQ pain domain demonstrates a high degree of content, criterion, and construct validity (Cronbach α = 0.88), high retest reliability (intraclass correlation coefficient = 0.86) and has been used as an outcome measure in clinical trials for a range of foot disorders [67]. Previous research indicates that the minimal important difference for this measure is 12.5 points [68]. The FHSQ pain domain will be measured at baseline and at 4, 8, 12 and 16 weeks, with the primary endpoint being the 16 week score.

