### Sample size

The sample size for the study has been calculated based on the pain domain of the FHSQ as the primary outcome measure [66]. Using a minimal important difference of 12.5 and a standard deviation of 23 obtained from a previous study [68], and assuming a 10% drop-out rate, the required sample size is 60 per group (power = 80%). We believe that the 10% drop-out rate is reasonable, as our recent randomized controlled trial of a multifaceted podiatry intervention to prevent falls in older people had a drop-out rate of less than 5% over a much longer period of follow-up (12 months) [71]. The extra precision provided by covariate analysis was conservatively ignored when performing this calculation.

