### Statistical analysis

Statistical analysis will be undertaken using SPSS version 20.0 (IBM Corp, NY, USA). All analyses will be conducted on an intention-to-treat principle using all randomized participants. Multiple imputation will be used to replace any missing data using five iterations, with age, baseline scores, and group allocation as predictors [72]. Demographic characteristics and baseline data will be summarized by descriptive statistics. Continuous data will be explored for normality using standard tests to satisfy the assumptions of parametric statistics. If data are found to be not normally distributed, transformation will be attempted using conventional techniques [73]. However, if data are still not normally distributed after transformation, non-parametric statistical tests will be used. Continuously-scored primary and secondary outcome measures with a normal distribution will be compared between groups using a linear regression technique with baseline scores, adjusted for by the analysis of covariance model [74,75]. Nominal and ordinal scaled data will be compared using chi-square analyses (or Fisher's exact test where appropriate) and Mann–Whitney *U*-tests, respectively. Effect sizes will be determined using Cohen’s *d*[76] for continuous data and relative risks for nominal data. Statistical significance for hypothesis tests will be set at the conventional level of α = 0.05.

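### The primary analysis depends on a normality test of the outcome, and the fallback may give up the baseline adjustment and the effect in FHSQ points

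*Protocol article*

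**What the plan says.** The Statistical analysis section sets an order of steps for continuous outcomes. The data are examined with unspecified standard normality tests. If they fail, conventional transformations are tried. After that, "if data are still not normally distributed after transformation, non-parametric statistical tests will be used". The parametric branch carries the same condition: "Continuously-scored primary and secondary outcome measures with a normal distribution will be compared between groups using a linear regression technique with baseline scores", adjusted by ANCOVA. The primary outcome falls under this rule and has no exemption.

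The same paragraph names Mann-Whitney tests for ordinal data, requires multiple imputation of missing data, and takes Cohen's d as the effect size for continuous data. It names no baseline-adjusted rank method.

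The primary outcome is the week-16 FHSQ pain score, built from four questions and running from 0 to 100. On its scale, "Previous research indicates that the minimal important difference for this measure is 12.5 points". The Sample size section uses that difference and adds that "The extra precision provided by covariate analysis was conservatively ignored when performing this calculation".

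**The concern.** The rule tests the wrong quantity. ANCOVA needs approximately normal residuals at most, and with some 54 to 60 participants per group the adjusted mean difference tolerates moderate departures even there. A bounded score from four questions can fail a formal test on the raw values while the model fits adequately.

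If the rule sends the primary outcome down the other branch, four things follow:

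- The method for the single primary comparison is settled by the trial's own outcome data, in a trial where participants and investigators are unblinded.
- An ordinary two-sample rank test leaves out the baseline score.
- Neither a rank test nor a transformed analysis yields an adjusted mean difference in FHSQ points to compare with 12.5. Cohen's d is in SD units and does not fill that place.
- A rank test fits poorly with multiple imputation. It supplies no estimate and variance to pool, and the completed data sets may not all pass or fail the normality test together.

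**Working it through.** **Inputs from the article.** Difference 12.5 and SD 23 ("Using a minimal important difference of 12.5 and a standard deviation of 23 obtained from a previous study"), power 80%, 60 per group, and "assuming a 10% drop-out rate". The significance level is 0.05; two-sided is assumed, since that reproduces the sample size.

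**Inputs not in the article, so assumed.** Correlation r between baseline and week-16 scores, 0 to 0.7; control mean, 35 to 65; score grid, either 6.25-point steps or continuous; normality test, Shapiro-Wilk or Lilliefors, applied to the pooled data or to each arm.

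**1. The plan's own figure.** n = 2 × (1.96 + 0.8416)² × 23² / 12.5² = 53.1, so 54 per group. 54 / 0.90 = 60. The stated sample size reproduces, and it is the size for an unadjusted comparison.

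**2. Power by method, 54 analysed per group.**

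- ANCOVA: SE = 23 × √(1 − r²) × √(2/54); power = Φ(12.5/SE − 1.96).
- Mann-Whitney, unadjusted, with efficiency 0.955: power = Φ(12.5 / [23 × √(2/(54 × 0.955))] − 1.96) = 78.8% at any r.

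| r | ANCOVA SE | ANCOVA power | Mann-Whitney power | Gap (points) |
|---|---|---|---|---|
| 0 | 4.43 | 80.6% | 78.8% | 1.8 |
| 0.3 | 4.22 | 84.1% | 78.8% | 5.3 |
| 0.5 | 3.83 | 90.3% | 78.8% | 11.5 |
| 0.7 | 3.16 | 97.7% | 78.8% | 18.9 |

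At r = 0.5 the gap splits into 90.3 − 80.6 = 9.7 points from losing the covariate and 80.6 − 78.8 = 1.8 points from using ranks. Only the second part comes out of the planned 80%.

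Simulation on the bounded 6.25-point grid at control mean 50 (2,000 runs per r) agrees: ANCOVA 79%, 82%, 89% and 97% for the four values of r, Mann-Whitney 77 to 78% throughout.

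**3. How often the fallback is reached.** Simulated trials with 54 per group, difference 12.5, SD 23 before clipping to 0–100, and r = 0.5 (400 runs per setting). The fallback counts only if the raw score and all five transformations tried (square root, log, square, reflected square root, reflected log) fail. Each range covers pooled and per-arm testing.

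| Control mean | Grid, Shapiro-Wilk | Grid, Lilliefors | Continuous, Shapiro-Wilk | Continuous, Lilliefors | ANCOVA residuals failing Shapiro-Wilk |
|---|---|---|---|---|---|
| 35 | 40–65% | 48–61% | 21–24% | 1–3% | 5% |
| 45 | 17–27% | 43–59% | 8–10% | 1–3% | 3–4% |
| 50 | 27–44% | 42–51% | 13–14% | 1–3% | 4–5% |
| 55 | 59–79% | 48–58% | 34–41% | 1–5% | 6–7% |
| 65 | 98–100% | 81–93% | 91–99% | 26–28% | 23–24% |

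On the grid, raw scores fail far more often than residuals do. With a continuous score the contrast depends on the test: it remains under Shapiro-Wilk, while Lilliefors seldom leads to the fallback.

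**4. Whether the branch matters.** At r = 0.5, ANCOVA and Mann-Whitney gave different significance verdicts in 13 to 16% of simulated trials, mostly with ANCOVA significant and Mann-Whitney not. With no true effect, ANCOVA rejected in 4 to 6% of trials, so bounds and discreteness did not disturb its error rate.

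**The case against.** The strongest reply is that little of what the trial promised is at risk. The sample size never counted on the covariate, so a rank test keeps nearly all of the planned power. The steps are ordered and written down in advance, and the endpoint is fixed at one time point. Simulated two-stage testing under no effect rejected in 3.7 to 6.0% of trials (400 runs per setting), which is consistent with 5%. The article does not name the fallback test for continuous data. An unadjusted Mann-Whitney test is an inference, and an analysis plan not shown here could specify something else. A non-parametric analysis can also report a Hodges-Lehmann shift, which is in FHSQ points.

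Most of this stands, and it limits the weight of the point. It does not remove it. The condition on ANCOVA is stated in the article, so an analysis plan could keep ANCOVA unconditionally only by departing from that text. A Hodges-Lehmann shift is not mentioned and would not by itself be adjusted for baseline.

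A reader might go further and infer that the trial will probably lose its ANCOVA, because a four-question bounded score will usually fail a normality test. The article does not support that. It gives no expected mean, score grid or named normality test, and those decide the answer. Near-certain rejection under Shapiro-Wilk appears at an assumed control mean of 65, where the treated arm presses on the ceiling. At mid-scale means the fallback is often the less likely branch.

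**Conclusion.** The point holds in a limited form. The article ties the primary method to a normality test of the outcome data instead of fixing it, and the rule may replace a sound baseline-adjusted model with an analysis that gives no adjusted difference in FHSQ points. The chance of this is unknown; about 1% to 100% is the range over the assumed settings. The cost to planned power is about 1 to 2 points. The cost in extra precision is about 10 power points at r = 0.5, and r is an assumption. No inflated type I error and no underpowered trial has been shown. The plan should be corrected, but the trial's validity does not hang on it. That the fallback is an unadjusted rank test is the natural reading, not a stated fact.

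**What to change.** Name one primary analysis, to be used whatever a normality test shows: ANCOVA of the untransformed week-16 FHSQ pain score on group and baseline score, with sex added because randomization is stratified by it (Design section). Report the adjusted mean difference in FHSQ points with its 95% CI, read against 12.5. This estimate and its variance also pool directly across the imputed data sets.

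Remove the sequence of normality test, transformation and non-parametric test for the primary outcome and the other scale scores. Inspect residuals. Use robust (HC3) or bootstrap standard errors, or a rank test, as sensitivity analyses only.

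The change is to wording and needs no further data or participants, but it should be made before outcomes are examined. The downside is a slight reliance on large-sample theory, which the sensitivity analyses cover.

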## Background

Foot pain affects approximately one in three people over the age of 65 years [1-3] and has a significant impact on quality of life in this age-group. Studies of older people have demonstrated that foot pain is associated with decreased ability to undertake activities of daily living [4-9], problems with balance and gait [7,10,11] and an increased risk of falls [12-16]. Furthermore, several clinic-based studies assessing health-related quality of life across a range of age-groups have shown that people with foot disorders (such as generalized foot pain [2,17], nail infections [18-20], hallux valgus [21,22] hallux rigidus [23] and plantar heel pain [24]) demonstrate significantly lower scores than those without these conditions. A range of risk factors for foot problems has been identified, including increased age [25-27], female sex [7,8,26,28], obesity [8,10,28,29], and chronic conditions such as osteoarthritis and diabetes [8,10,29].

In addition to these risk factors, there is also strong evidence that many older people wear inappropriate or poor quality footwear, and that ill-fitting footwear may contribute to foot problems. A household survey of people aged over 80 years conducted in the United Kingdom found that most wore slippers all day, irrespective of whether they were housebound [30]. Similarly, a survey of the indoor shoe-wearing habits of 128 older people in Australia indicated that more than half spent less than 30 Australian dollars on their indoor footwear (most commonly slippers), replaced them infrequently, and often wore their indoor shoes for outdoor activities [31]. More recently, a survey of sub-acute aged care hospital patients reported that only 14% wore ‘safe’ footwear, with the most commonly observed detrimental features being a lack of fastening (86%), slippery soles (86%) and an excessively flexible heel counter (77%) [32].

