## Design

This study is a two-group randomized controlled trial with a 16 week prospective follow-up (Figure 1). Participants will be randomly allocated to either a ‘usual care’ control group or the intervention group [47]. Permuted block randomization with random block sizes (stratified by sex [48]) will be undertaken using an interactive voice response telephone service provided by the NHMRC Clinical Trials Centre at the University of Sydney, New South Wales, Australia to ensure allocation concealment. Due to the nature of the intervention, it will not be possible to blind the participants or investigators. However, the primary outcome measure is administered as a self-completion questionnaire and will be entered into the database by an investigator blinded to group allocation.

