### Intervention group

The intervention group will continue to receive regular podiatry treatment as clinically required. This will typically include toenail maintenance and scalpel debridement of hyperkeratotic lesions (corns and calluses). In addition, they will be provided with good quality, off-the-shelf footwear ([name]® Vasyli Medical, Labrador, Queensland, Australia). Men will receive the ‘Brian’ style and women will receive the ‘Annie’ style (see Figures 2 and 3). Both styles are available in three width fittings (medium, wide, extra-wide) and feature a stretchable Lycra® upper with Velcro® closure and a removable, flat cushioned insole. These shoes have been selected as they meet all commonly-used criteria for appropriate footwear (such as a low heel, appropriate fixation and adequate depth to accommodate toe deformities) [53-57]. Due to sex differences in foot dimensions (and therefore the dimensions of the lasts the shoes are constructed from) the ‘Brian’ style has a relatively broader fit than the ‘Annie’ style. However, both the heel height and toe spring are the same for shoes of equivalent length across the two styles.

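### Randomisation is stratified by sex, but the stated ANCOVA and imputation model leave sex out, so the reported standard error may be slightly too wide

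*Protocol article*

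**What the plan says.** In the Protocol article, the Design section describes the allocation as "Permuted block randomization with random block sizes (stratified by sex [48"; sex is the only stratification factor named. The Statistical analysis section says that normally distributed continuous outcomes, primary and secondary, will be analysed "using a linear regression technique with baseline scores, adjusted for by the analysis of covariance model". No covariate other than the baseline score is named. Missing data are to be multiply imputed "with age, baseline scores, and group allocation as predictors", so sex is absent there too.

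Two other places bear on the point. The Background states: "A range of risk factors for foot problems has been identified, including increased age [25-27], female sex". The Sample size section says that any precision gained from covariates was left out of the calculation. Sex is recorded under Baseline assessments. No section says that sex will be adjusted for.

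**The concern.** Stratified blocks keep the two arms nearly balanced on sex, so differences between men and women contribute almost nothing to the sampling error of the treatment effect. A model without sex does not know this. It counts the between-sex variation as residual noise and reports a standard error larger than the estimate's true sampling variability. Confidence intervals are then wider than they need to be, and the test rejects less often than its nominal 5% under the null.

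This happens only if sex predicts the 16-week score after the baseline score has been taken into account. The article gives no figure for that. What supports a non-zero effect is the Background statement on risk factors and the choice of sex as the sole stratifier.

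**Working it through.** **The plan's own sample size.** Inputs from Sample size: difference 12.5, SD 23, power 80%, drop-out 10%. From Statistical analysis: "Statistical significance for hypothesis tests will be set at the conventional level of α = 0.05". Sidedness is not stated; two-sided is assumed.

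n per arm = 2 × 23² × (1.96 + 0.8416)² / 12.5² = 53.1, rounded up to 54. Then 54 / 0.90 = 60. The stated 60 per group is reproduced, and it does not depend on any covariate.

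**Assumptions for the check** (none is in the article): SD 23 within each sex, baseline-outcome correlation 0.5, half the participants women, 54 completers per arm. The size of the sex gap after baseline adjustment is unknown, so it is varied.

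Residual variance given baseline and sex = 529 × (1 − 0.5²) = 396.75.

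True standard error = √(396.75 × 2/54) = 3.83.

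Ratio of reported to true standard error without sex: k = √(1 + p(1 − p) × gap² / 396.75), with p the share of women. For a gap of 10: √(1 + 0.25 × 100/396.75) = 1.031.

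True type I error = 2 × [1 − Φ(1.96k)]. Power without sex = Φ(12.5/3.83 − 1.96k). Power with sex sets k = 1.

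| Residual sex gap (points) | Reported SE too wide by | True type I error | Power without sex | Power with sex |
|---|---|---|---|---|
| 0 | 0% | 5.0% | 90.3% | 90.3% |
| 5 | 0.8% | 4.8% | 90.1% | 90.3% |
| 10 | 3.1% | 4.3% | 89.3% | 90.3% |
| 15 | 6.9% | 3.6% | 87.8% | 90.3% |
| 20 | 11.9% | 2.8% | 85.7% | 90.3% |

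The last two rows need a residual sex gap larger than the 12.5-point minimal important difference, so they mark the upper end. The excess also shrinks when the sexes are unevenly represented: with 10% women it is 1.1%, 2.5% and 4.4% at gaps of 10, 15 and 20.

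**Simulation of the mechanism.** Sex-stratified permuted blocks (sizes 2, 4 and 6 assumed), 108 completers, 4,000 runs per row, no treatment effect:

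| Gap | Without sex: mean reported SE / actual SD | Rejects | With sex: mean reported SE / actual SD | Rejects |
|---|---|---|---|---|
| 0 | 3.84 / 3.87 | 5.2% | 3.84 / 3.87 | 5.2% |
| 5 | 3.88 / 3.78 | 3.9% | 3.85 / 3.78 | 4.0% |
| 10 | 3.96 / 3.84 | 4.1% | 3.84 / 3.84 | 4.7% |
| 15 | 4.11 / 3.86 | 3.9% | 3.84 / 3.85 | 5.3% |
| 20 | 4.30 / 3.79 | 2.5% | 3.84 / 3.78 | 4.4% |

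Simulation error on a 5% rejection rate is √(0.05 × 0.95/4000) = 0.3 percentage points, so the comparison between models within a row is more informative than either rate alone. The actual SD is virtually the same with and without sex at every gap; only the reported SE moves.

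**Sensitivity to the baseline correlation.** Take a correlation of zero and let 23 be the total SD, as the sample size calculation does. If sex explains 2%, 5% or 10% of the variance, the reported SE is too wide by 1.0%, 2.6% or 5.4% (1/√(1 − R²)). Power without sex is 80.9%, 81.2% or 81.9%, against 81.4%, 82.6% or 84.5% with it. If instead 23 is the within-sex SD and the correlation is zero, a 10-point gap gives 79.3% without sex and 80.6% with it. In that case the total SD is already above the planned value: √(529 + 25) = 23.5.

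**The case against.** The strongest reply is that the harm is conditional and may be nil. The Background speaks of risk factors for having foot problems. It does not say that sex predicts the 16-week score given baseline pain, among people all selected for persistent, disabling foot pain. Baseline adjustment already absorbs much of any sex difference in pain level, and with no residual gap the two models agree. This stands: the omission is certain, its cost is not.

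It can also be said that a journal article condenses the plan and does not state that baseline is the only covariate, so a fuller list may exist elsewhere. This carries limited weight, because the article does name its ANCOVA covariate and does list its imputation predictors, and the stratifier is in neither place.

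Three stronger readings are tempting and are not supported.

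- A reader might infer that the benefit of stratification is lost, as if participants had been discarded. The simulated sampling SD at a 15-point gap is 3.86 without sex and 3.85 with it, so the estimate keeps its precision and only the reported interval is too wide.
- A reader might take the different shoe styles for men and women (Intervention group section: one "style has a relatively broader fit than the" other) as evidence that sex is prognostic. That difference bears on whether the treatment effect varies by sex. It says nothing about outcome in controls, who receive no study shoes until the end, and a main effect of sex would not address it.
- A reader might extend the point to the binary and count outcomes. The calculation covers linear models only.

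**Conclusion.** The mismatch between a sex-stratified design and an analysis that names only the baseline score is in the text. Its consequence is small and one-directional: if sex is prognostic beyond baseline, reported standard errors are too wide and tests mildly conservative. For residual gaps up to 10 points, under the assumptions above, this means up to about 3% excess in the standard error and about 1 point of power.

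Nothing in the plan is invalidated. The treatment estimate is unbiased and type I error is not inflated. The planned 60 per group stands, and the 80% target is not threatened if 23 is the total SD or if baseline is moderately correlated with outcome. The figures rest on the assumed correlation, share of women and sex gap, none of which the article gives. This is a low-cost improvement worth making, not a correction on which the trial's conclusion depends.

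**What to change.** In the Statistical analysis section, pre-specify sex as a covariate alongside the baseline score in the ANCOVA for the primary outcome and for the continuous secondary outcomes analysed that way. Add sex to the multiple-imputation predictors at the same time: values imputed without a covariate that the analysis model contains dilute that covariate's estimated effect.

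The cost is one degree of freedom. With 108 completers, the residual degrees of freedom fall from 105 (108 minus intercept, group and baseline) to 104. Sex is already collected at baseline, so no new data are needed and the sample size does not change. Stating the adjustment in advance also removes later discretion over whether to make it.

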### Baseline assessments

Participant characteristics will be collected by structured interview at the baseline assessment and will include age, sex, height, weight, waist circumference, hip circumference, country of birth, education, major medical conditions, medications, use of walking aids and cigarette smoking history. The following questionnaires and clinical tests will also be administered:

(i) foot pain characteristics, including duration (in months) and location, using a standardized foot diagram;

(ii) presence and severity of hallux valgus, assessed using the Manchester Scale [59];

(iii) foot structure and presence of hyperkeratotic lesions (corns and calluses), documented with three-dimensional clinical photographs using the FotoScan™ 3D foot scanner (Precision 3D Limited, Weston-super-Mare, UK);

(iv) the Pain Catastrophizing Scale, a questionnaire containing 13 items reflecting elevated negative cognitive responses to pain [60];

(v) the short version of the Geriatric Depression Scale, a 15-item depression screening tool that has been specifically validated in older people [61,62];

(vi)  footwear assessment, using selected components of the recently developed Footwear Assessment Tool [57], and;

(vii)  physical activity levels, using the Incidental and Planned Activity Questionnaire [63].

In addition, participants allocated to the footwear intervention group will be asked to complete six 100 mm visual analogue scales to ascertain their perceptions of: (i) the immediate level of comfort of the footwear (using the anchors ‘extremely uncomfortable’ and ‘extremely comfortable’ [64]); (ii) the attractiveness of the footwear (using the anchors ‘extremely unattractive’ and ‘extremely attractive’); (iii) how attractive they think other people would find the footwear (using the anchors ‘extremely unattractive’ and ‘extremely attractive’); (iv) how well the shoes fit (using the anchors ‘poorest fit possible’ and ‘best fit possible’); (v) how easy it is to put the shoes on and take them off (using the anchors ‘most difficult as possible’ and ‘as easy as imaginable’) and; (vi) how heavy the shoes are (using the anchors ‘extremely light’ and ‘extremely heavy’).

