### Secondary outcome measures

Secondary outcome measures will be documented at baseline and 16 weeks and will include:

(i) the function domain of the FHSQ [3];

(ii) the functional limitation, pain intensity and concern about appearance subscales of the MFPDI [49];

(iii) the number of DVA podiatry treatments required during the study period;

(iv) general health-related quality of life, assessed with the Short Form 12® Version 2.0 [69];

(v) the number of falls experienced during the follow-up period;

(vi) functional mobility, using the Timed Up and Go test [70];

(vii) presence of hyperkeratotic lesions (corns and calluses);

(viii) number of participants using co-interventions to relieve foot pain (such as oral non-steroidal antiinflammatory medications, topical medications and visits to other health-care practitioners), documented using a diary at 4, 8, 12 and 16 weeks, and;

(ix) participants’ perception of overall treatment effect at week 16, assessed with the question ‘Overall, how has your foot pain changed since the start of the study?’ with a five-point Likert scale response (‘marked worsening’, ‘moderate worsening’, ‘same’, ‘moderate improvement’, or ‘marked improvement’). For the purpose of analysis, this scale will then be dichotomized, where ‘success’ is defined as marked or moderate improvement on this scale.

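### Corns and calluses are recorded at baseline, but the planned 16-week test of lesion presence ignores baseline status and gives up precision, by an amount the documents do not fix

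*Protocol article*

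**What the plan says.** Under Secondary outcome measures, the article states that "Secondary outcome measures will be documented at baseline and 16 weeks and will include" nine items. Item (vii) is "presence of hyperkeratotic lesions (corns and calluses"). The Baseline assessments section confirms that the starting value is collected: "foot structure and presence of hyperkeratotic lesions (corns and calluses), documented with three-dimensional clinical photographs".

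The Statistical analysis section treats the two types of outcome differently. For continuous outcomes: "Continuously-scored primary and secondary outcome measures with a normal distribution will be compared between groups using a linear regression technique with baseline scores" as the adjustment. For categorical outcomes: "Nominal and ordinal scaled data will be compared using chi-square analyses", with Fisher's exact test where needed, Mann–Whitney tests for ordinal data, and "relative risks for nominal data" as the effect measure. Neither the chi-square nor the Fisher test carries a covariate. Apart from the continuous-outcome model, baseline scores appear in that section only as predictors for multiple imputation.

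The Sample size section acknowledges that covariate analysis adds precision and says this was left out of the calculation to be conservative.

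**The concern.** Lesion presence is a yes/no outcome measured twice on the same person. If a participant with a callus at baseline is more likely than others to have one at 16 weeks, part of the variation in the 16-week result is already explained by a value in hand. The plan uses that information for continuous outcomes and discards it here. This is a commitment in the text and not a detail left open: a later analysis plan that adjusted would depart from the published wording.

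Precision is at stake for one secondary outcome, as is how readily the result can be read if the arms happen to differ in baseline lesions. The Design section stratifies randomization by sex only, so nothing in the design balances lesion status.

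**Working it through.** **The plan's own figure.** The Sample size section uses a difference of 12.5, SD 23, 80% power and 10% drop-out. With two-sided α = 0.05 (sidedness is not stated; two-sided reproduces the figure), n = 2 × (1.960 + 0.842)² × 23² / 12.5² ≈ 53.2, so 54 per group, and 54 / 0.9 = 60. The stated 60 per group is reproduced. It concerns FHSQ pain only; no power is stated for lesions. I use 54 analysed per group below.

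**Assumed inputs.** The documents give no lesion prevalence, persistence or effect. Let π be baseline prevalence, and p₁ and p₀ the chance of a lesion at 16 weeks with and without one at baseline.

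**Why adjustment helps.** The unadjusted comparison has variance m(1−m)/n in each arm, where m = πp₁ + (1−π)p₀. Adjusting for baseline leaves only the within-stratum part, [πp₁(1−p₁) + (1−π)p₀(1−p₀)]/n.

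Strong persistence: π = 0.65, control 0.85/0.15, treated 0.60/0.08.
- m = 0.605 and 0.418; difference 0.187.
- Unadjusted SE = √[(0.2390 + 0.2433)/54] = 0.0945, z = 1.98, power about 51%.
- Adjusted SE = √[(0.1275 + 0.1818)/54] = 0.0757, z = 2.47, power about 70%.

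Weak persistence: π = 0.65, control 0.70/0.30, treated 0.50/0.18.
- m = 0.560 and 0.388; difference 0.172.
- Unadjusted SE = √[(0.2464 + 0.2375)/54] = 0.0947, z = 1.82, power about 44%.
- Adjusted SE = √[(0.2100 + 0.2142)/54] = 0.0886, z = 1.94, power about 49%.

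**Simulation.** The hand figures are large-sample approximations. Simulation (40,000 trials per setting, 54 per group) compared the Pearson chi-square with a Mantel–Haenszel test stratified by baseline lesion status:

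| Prevalence | Control p₁/p₀ | Treated p₁/p₀ | Chi-square | Stratified |
|---|---|---|---|---|
| 65% | 85%/15% | 60%/8% | 47% | 68% |
| 65% | 90%/15% | 65%/8% | 48% | 73% |
| 65% | 70%/30% | 50%/18% | 41% | 48% |
| 65% | 70%/30% | 45%/20% | 52% | 58% |
| 65% | 60%/30% | 40%/18% | 44% | 47% |
| 95% | 85%/15% | 60%/8% | 79% | 83% |

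A wider grid used prevalence of 50, 70 and 85%, control persistence from 95%/5% down to 60%/40%, and effects set to give the chi-square 50% or 80% power. Gains ran from about 1 to about 42 points: 1 to 7 at 70%/30% or weaker, 7 to 16 at 80%/20%, and 12 to 42 at 90%/10% or stronger. Adjustment lost power in no setting.

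**Validity.** With no treatment effect, the chi-square rejected in 4.2 to 5.2% of simulated trials, so its error rate holds.

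**Chance imbalance.** At 65% prevalence, the SD of the baseline difference is √(2 × 0.65 × 0.35 / 54) = 0.092. The arms differ by 10 or more points in about 27% of trials. Within those trials, under no effect, the chi-square rejects about 14% of the time at 85%/15% persistence and about 7.5% at 70%/30%. The overall rate remains near 5%.

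**The case against.** The best case for the plan is that nothing in it is invalid. Chi-square is a proper test under randomization, its 5% error rate already allows for chance imbalance, and this is one of nine secondary outcomes in a trial powered for FHSQ pain alone. All of that stands. The point is one of efficiency, and the imbalance figures describe how a single trial may read, not bias in the design.

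It also stands that the size is unknown. Both arms continue podiatry that typically includes scalpel removal of corns and calluses (Intervention group and Control group sections). The timing of that care could loosen the link between baseline and 16-week status. Very high prevalence also shrinks the gain.

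The simulated test was Mantel–Haenszel. Modified Poisson and standardised logistic analyses were not simulated, so their gain is expected to be similar but was not measured.

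A reader might infer several stronger points that the documents do not support:
- *Baseline status is the strongest predictor and most of the power is lost.* No document ranks predictors or gives persistence.
- *Lesions are rated unblinded.* The Design section says "Due to the nature of the intervention, it will not be possible to blind the participants or investigators", but the Discussion narrows this to investigators providing the intervention, and no section says who rates lesions. Photographs are specified only at baseline, so scoring of paired images cannot be assumed.
- *Chi-square results cannot be combined over imputations.* Combination rules for chi-square statistics exist, and the log of the promised relative risk pools by Rubin's rules.
- *Lesions are the mechanism by which the shoes cut podiatry need.* The Background says only that footwear may reduce maintenance care.

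**Conclusion.** The concern holds as a minor efficiency point. The plan collects baseline lesion status, adjusts comparable continuous outcomes for baseline, and then commits lesion presence to an unadjusted test. The test keeps its error rate.

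With 54 per group and 65% prevalence, the power given up is about 3 to 7 points under weak persistence (70%/30% or weaker) and about 20 to 30 points under strong persistence (85 to 90%). Prevalence, persistence and effect are all assumed, as is a two-sided "Statistical significance for hypothesis tests will be set at the conventional level of α = 0.05". The direction is secure across every setting tried; the size is not. The primary outcome and the sample size are unaffected.

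**What to change.** In the Statistical analysis section, or in the analysis plan as a stated change, take lesion presence out of the chi-square sentence and add wording such as: presence of hyperkeratotic lesions at 16 weeks will be compared between groups by a regression for binary data adjusted for baseline lesion presence and sex, giving an adjusted relative risk with 95% confidence interval, pooled over the imputed datasets on the log scale.

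Name one method before the data are examined: modified Poisson with robust standard errors, or logistic regression with standardisation. A Mantel–Haenszel relative risk stratified by baseline lesion status is a simpler alternative. Sex belongs in the regression because it is the stratification factor. The raw counts and unadjusted relative risk can still be shown beside it.

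The cost is slightly more analysis work. No extra participants, visits or measurements are needed.
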